### Statistical analysis

2.7

All analyses will be performed using SPSS for Windows, version 16, and GraphPad InStat. Analysis of variance is used for comparing mean values of patient's age, weight, height, and body mass index. For nonparametric measures such as pain score and functional scores, differences between baseline and posttreatment scores for each group are computed by the Wilcoxon signed ranks test. The difference between each treatment group is performed by the Kruskal--Wallis test. The level of statistical significance is set as *P* < .05. A power analysis is conducted to estimate the requisite sample size. From preliminary research in our hospital, a clinically significant difference reduction in the pain score was defined as 3 cm; a standard deviation of 3.49, probability of a Type I error of 0.05, and power of 0.8 resulted in an estimated sample size of 25. Consequently, a total of 90 subjects will be recruited.

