### Outcomes parameters

2.6

All patients will be assessed for pain and functional status before and immediately after the treatment by a researcher blinded to the patient groups. The range of shoulder mobility and functional status will be assessed using the Constant Shoulder Scale, which was developed to evaluate functional recovery of the shoulder. The total Constant score ranges from 0 to 100 points, with higher scores indicative of better function. The score is divided into four sections: pain (15 points), activities of daily living (20 points), range of motion (40 points), and strength (25 points). Pain is scored using a visual analog scale. The activities of daily living score are divided into 4 subscales of sleep, work, recreational activities, and ability to position the hand in space. Range of motion is assessed in 4 active positions, with 10 points for each. Flexion and abduction are assessed by a goniometer, whereas functional internal and external rotation is assessed by the position of the hand. Strength is tested by a calibrated spring dynamometer, at 90° abduction of the shoulder with the forearm pronated and scored as the maximum of 3 repetitions (Tables 1 and 2).

**Table 1 T1:** Patient baseline demographics.

Demographics	Combined group	PRF lesioning of the SNN group	Ultrasound group	*P*
Number of patients (shoulders)				
Age, yr				
Male sex [no. (%)]				
BMI^∗^, kg/m^2^				
Left side [no. (%)]				
Follow-up^∗^				

BMI = body mass index, PRF = pulsed radiofrequency, SSN = suprascapular nerve.

∗ The values are given as the mean and the SD.

**Table 2 T2:** Postoperative outcomes.

Outcomes	Combined group	PRF lesioning of the SNN group	Ultrasound group	*P*
VAS				
Constant score				
Range of motion				
Muscle strength				

PRF = pulsed radiofrequency, SSN = suprascapular nerve, VAS = visual analog scale. The values are given as the mean and the SD.

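### Baseline scores enter explicitly only through uncontrolled within-arm tests; the valid between-arm Kruskal-Wallis test states no baseline adjustment, and an ANCOVA would be more precise

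*Protocol article*

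**What the plan says.** Section 2.6 (Outcomes parameters) has pain and function measured in every patient before treatment and immediately after it, so a baseline value exists for each score.

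Section 2.7 (Statistical analysis) names two tests for these scores. One works within each arm and covers pain and function, which the text treats as nonparametric: "differences between baseline and posttreatment scores for each group are computed by the Wilcoxon signed ranks test". Next comes a Kruskal-Wallis test between the treatment groups. The sentence that introduces it does not say which variable is ranked and does not mention baseline.

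Table 2 lists postoperative VAS, Constant score, range of motion and strength by arm, with a single P column and no column for baseline or change. Its footnote says "The values are given as the mean and the SD".

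The power statement in the same section reads "a clinically significant difference reduction in the pain score was defined as 3 cm", with "a standard deviation of 3.49" and "probability of a Type I error of 0.05, and power of 0.8"; this "resulted in an estimated sample size of 25", and "a total of 90 subjects will be recruited". It does not say whether the SD belongs to the post-treatment score or to the change.

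**The concern.** The trial asks a comparative question: does the combination do better than either treatment alone? A signed-rank test inside one arm compares patients with their own past. Natural course and regression to the mean are mixed with any treatment effect, and no arm serves as the control for that test. If the arms give different significance results, this is not evidence that they differ. If all are significant, this is not evidence that any of them works. No arm is untreated, so the second pattern could easily be read as three effective treatments.

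The between-arm test does address the question. As described, though, it makes no stated use of the baseline score as a covariate. If post-treatment scores are ranked, the baseline information is unused and chance imbalance in arms of about 30 goes uncorrected. If changes are ranked, baseline is used, but with a fixed weight that is usually not the efficient one.

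**Working it through.** **Inputs.** From section 2.7: difference 3 cm, SD 3.49, alpha 0.05 (taken as two-sided), power 0.80, stated n of 25 (read as per arm), total 90. Equal allocation is assumed, so 90/3 = 30 per arm. The baseline-to-post correlation r is not given; 0.3, 0.5 and 0.7 are assumed. Baseline and post-treatment variances are assumed equal.

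**Step 1: the plan's own figure.** Standardised difference d = 3/3.49 = 0.860.
- Normal approximation: n = 2 × [3.49 × (1.960 + 0.842)/3]² = 21.2, so 22 per arm.
- Exact two-sample t-test: 22.25, so 23 per arm.
- t-test n divided by a rank-test efficiency of 0.955 or 0.864: 23.3 or 25.7, so 24 to 26 per arm.

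The stated 25 is therefore reproduced as a per-arm number.

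**Step 2: between-arm precision, with 3.49 as the SD of the post-treatment score.** Variance relative to the post-treatment comparison is 1 for post scores, 2(1 − r) for change scores and 1 − r² for ANCOVA. Power is that of a two-sided two-sample t-test with effect d/√factor.

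| r | Change factor | ANCOVA factor | Post, n = 30 | Change, n = 30 | ANCOVA, n = 30 |
|---|---|---|---|---|---|
| 0.3 | 1.40 | 0.91 | 0.906 | 0.790 | 0.929 |
| 0.5 | 1.00 | 0.75 | 0.906 | 0.906 | 0.966 |
| 0.7 | 0.60 | 0.51 | 0.906 | 0.988 | 0.996 |

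At r = 0 the ANCOVA factor is 1 and nothing is gained over post scores. At 25 per arm, post scores give 0.846 and ANCOVA 0.877/0.930/0.986. The gain looks larger there, but 30 is the planned size.

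**Step 3: with 3.49 as the SD of change.** The ANCOVA residual SD is 3.49 × √((1 + r)/2) = 2.81/3.02/3.22. At 30 per arm, power is 0.982/0.966/0.944, against 0.906 for change scores.

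**Step 4: check against the planned test.** Step 2 uses t-tests, not Kruskal-Wallis. A simulation of three arms of 30 (normal data, means 0, 1.5 and 3, SD of the post-treatment score 3.49, 2,000 runs per scenario) gave, for r = 0.3/0.5/0.7:
- Kruskal-Wallis on post scores: 0.82/0.83/0.82
- Kruskal-Wallis on change: 0.68/0.82/0.96
- ANCOVA: 0.87/0.93/0.98

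With no true difference, ANCOVA rejected in 4.7% to 5.9% of runs across the scenarios with 25 or 30 per arm, consistent with 5% within simulation error.

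**Step 5: what the within-arm tests do when the arms are identical.** Suppose all three arms improve by the same amount (SD of change assumed 3.49, normal data, 30 per arm). If each Wilcoxon test is significant with probability p, the three disagree with probability 1 − p³ − (1 − p)³, which cannot exceed 75% (at p = 0.5).

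| Common improvement | p | Tests disagree |
|---|---|---|
| 0.5 cm | 0.12 | about 30% |
| 1.3 cm | 0.49 | about 75% |
| 2 cm | 0.85 | about 40% |
| 3 cm | 0.99 | 2 to 3% |

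At 3 cm, all three are significant in about 98% of trials. The treatments are the same in every row, and no row says anything about a difference between them.

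**The case against.** The plan does contain a between-arm test, and it is sound. Section 2.7 gives the treatment comparison to Kruskal-Wallis, and Table 2 has one P column across arms and none for within-arm tests. A reader might infer that arms will be ranked by whose Wilcoxon test is significant, or that there is no between-arm comparison at all. The article says neither. Nor is it established that baseline is ignored between arms: the Kruskal-Wallis sentence follows one about baseline-to-post differences, and the sample size rests on a reduction in pain. Table 2 points the other way, to postoperative values. The text is open on this.

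A reader might also take 75% disagreement as typical. It is the maximum of the range; at the protocol's own 3 cm the figure is 2 to 3%.

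Sizing on a mean difference and SD, then testing by ranks and tabulating mean and SD, may look contradictory. It is common practice, and the stated 25 fits a rank-inflated t-test calculation, so this is not a fault.

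Finally, covariate adjustment is often left to an analysis plan, the scores are bounded, and ANCOVA moves from a rank comparison to a comparison of means. These points limit how serious the matter is. They do not remove it: the article names its tests, none is stated to adjust for baseline, and the within-arm tests do not serve the comparative aim.

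**Conclusion.** The point holds as one of efficiency and interpretation. The within-arm Wilcoxon tests cannot show that one treatment is better. The Kruskal-Wallis test is valid under randomisation, but its input is unnamed and no baseline adjustment is stated.

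At 30 per arm, ANCOVA raises pairwise power over post scores by about 2, 6 and 9 percentage points at r = 0.3, 0.5 and 0.7, and over change scores by about 14, 6 and 1 points, with 3.49 read as the SD of the post-treatment score. In the three-arm simulation the gain over Kruskal-Wallis on post scores is about 5 to 16 points. These sizes rest on the assumed r, equal allocation, equal variances and roughly normal scores. The direction over this range does not depend on which input the Kruskal-Wallis test was meant to have. The change should be made, but the trial's between-arm conclusion would not be invalid without it.

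**What to change.** In section 2.7:

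- Present within-arm change descriptively, with confidence intervals and no inferential P values.
- Make the main analysis of VAS pain and Constant score an ANCOVA of the post-treatment value on treatment arm and the baseline value of the same score. Report adjusted mean differences with 95% CIs for the combined arm against each single arm.
- Keep Kruskal-Wallis, with its input named as post-treatment score or change, or a rank-based ANCOVA, as a sensitivity analysis for skewed or bounded scores.
- Add baseline values and adjusted differences to the results table.

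The cost is wording. No extra patients, visits or measurements are needed. The statistical price is one degree of freedom, trivial with 90 patients, and a main result stated as a difference in means instead of ranks.

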Physical therapy agents including superficial and deep heat with analgesic currents are commonly used to decrease pain and spasm owing to adhesive capsulitis. Rehabilitation methods, including stretching, range of motion, strengthening exercises, and mobilization maneuvers are used to improve joint mobility and restore function. However, these interventions are usually painful and prevent the individual from fully participating in the rehabilitation program. Therefore, PRF lesioning of the SSN may be preferred for adhesive capsulitis before applying physical therapy.^[11,12]^

To our knowledge, there have been no published clinical trial to assess the synergistic effects of applying PRF stimulation of the SSN plus physical therapy on pain and function in patients with adhesive capsulitis. Therefore, we will conduct this present randomized, double-blind study to evaluate the synergistic effects of applying PRF stimulation of the SSN plus physical therapy on pain and function in patients with adhesive capsulitis. It is assumed that there will be a remarkable difference in postoperative outcomes between the intervention and control groups.

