### Recruitment and randomization

2.3

Recruitment will be started in March 2021 and completed in October 2022. The treating surgeon will assess 90 patients for eligibility. Written informed consent will be obtained from patients. Then, each patient will be randomized into 3 treatment groups, receiving PRF stimulation of the SSN or physical therapy or both of them. To allocate treatment, a randomization sequence with random permuted blocks will be generated by randomization program on internet website (www.randomizer.org). Sequentially numbered opaque sealed envelopes containing treatment allocations will be prepared and opened in sequence by an independent research assistant who is not involved in treatment. All the data collectors, surgeons, statistical analysts, as well as result assessors are not aware of grouping assignment (Fig. 1).

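### The single three-group Kruskal-Wallis P per outcome tests whether any arm differs, not whether the combination beats each of its components

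*Protocol article*

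**What the plan says.** The Introduction gives the aim as to "evaluate the synergistic effects of applying PRF stimulation of the SSN plus physical therapy on pain and function". Under Recruitment and randomization, "each patient will be randomized into 3 treatment groups, receiving PRF stimulation of the SSN or physical therapy or both of them". There is no arm with neither treatment.

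The Statistical analysis section names three tests:

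- For age, weight, height and body mass index: "Analysis of variance is used for comparing mean values of patient's age, weight, height, and body mass index". This does not touch outcomes.
- Within each arm, for pain and functional scores: "differences between baseline and posttreatment scores for each group are computed by the Wilcoxon signed ranks test". This is not a comparison between arms.
- Between arms: "The difference between each treatment group is performed by the Kruskal--Wallis test". No pair of arms is named.

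The threshold is a single one: "The level of statistical significance is set as *P* < .05". Table 2 has three arm columns and one P column, and its footnote reads "The values are given as the mean and the SD". It has no column for a difference between arms. (Its third arm is labelled as an ultrasound group. I read this as the physical therapy arm.)

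**The concern.** The aim is about the combination against its parts, so it needs two comparisons: combined versus PRF alone, and combined versus physical therapy alone. A Kruskal-Wallis test over three arms makes neither. Its null hypothesis is that all three distributions are the same, and any departure counts against it, including one in which the two single treatments differ and the combination only matches the better of them. The sentence that assigns it the job of giving the difference between the arms therefore misdescribes what it delivers, and the one-P layout of Table 2 confirms that a single omnibus result per outcome is planned.

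At stake is the headline result. A significant P could come from a trial in which adding one treatment to the other gained nothing, and nothing in the stated analysis would distinguish that from success.

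**Working it through.** **Inputs.** From Statistical analysis: difference 3 cm, SD 3.49, type I error 0.05, power 0.8, stated sample size 25, total 90. Assumed, because not stated: 1:1:1 allocation (90 / 3 = 30 per arm), two-sided tests, normal data with a common SD.

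**1. The plan's own figure.** For two groups, n per arm = 2 × [SD × (1.960 + 0.842) / difference]² = 2 × (3.49 × 2.802 / 3)² = 21.24, so 22.

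- The two-sample t-test version gives 22.25, so 23.
- Dividing 21.24 by 0.864, the worst-case efficiency of a rank test, gives 24.59, so 25.

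The stated 25 therefore reproduces as a per-arm number for a comparison of two arms. The sizing is pairwise and the stated analysis is not.

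**2. What drives the Kruskal-Wallis test.** For normal data its power depends approximately on λ = 0.955 × n × S / SD², where S is the sum of squared deviations of the three arm means from their average and SD² = 3.49² = 12.18. Write the mean improvement as (combined, PRF, therapy):

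- Combined equals PRF, therapy 3 cm worse, (3, 3, 0): average 2, S = 1 + 1 + 4 = 6.
- Combined 3 cm better than both, (3, 0, 0): average 1, S = 4 + 1 + 1 = 6.
- Combined halfway between PRF (better) and therapy, (1.5, 3, 0): average 1.5, S = 0 + 2.25 + 2.25 = 4.5.

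The first two cases have the same S, so the test is about equally likely to be significant in both. At S = 6, λ = 0.955 × 25 × 6 / 12.18 = 11.76 at 25 per arm and 14.11 at 30. On 2 degrees of freedom this gives approximate power of 88% and 93%.

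**3. Simulation** (20,000 trials per scenario; pairwise tests are Mann-Whitney at two-sided 0.05):

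| True improvement (combined, PRF, therapy) | n per arm | Kruskal-Wallis P < .05 | Combined found better than PRF |
|---|---|---|---|
| (0, 0, 0) | 25 / 30 | 5% / 5% | 2% / 2% |
| (3, 3, 0) | 25 / 30 | 86% / 92% | 2% / 2% |
| (3, 0, 0) | 25 / 30 | 86% / 92% | 82% / 89% |
| (1.5, 3, 0) | 25 / 30 | 74% / 82% | below 0.1% |

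The omnibus column cannot tell row 2 from row 3; the named contrast can. In row 4 the combination is truly worse than PRF alone, and the omnibus test is still significant in about three quarters of trials or more.

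**4. Error rate of pairwise tests.** Under (0, 0, 0), at least one of three unadjusted pairwise tests is significant in about 11.5 to 12% of trials if they are run regardless. If they are run only after a significant Kruskal-Wallis result, the rate is about 5%.

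**5. Power after the fix.** Under (3, 0, 0), both Mann-Whitney contrasts are significant in about 71% of trials at 25 per arm and 81 to 82% at 30, varying slightly between simulation runs.

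**The case against.** **Pairwise tests may sit elsewhere.** This is a condensed article; follow-up comparisons and interval estimates are often left to a fuller document, and the sentence's wording about each group may have been meant pairwise. It stands that omitting such detail would be no fault by itself. But this article does not leave the matter open: it names the between-group test and lays out the results table, and both fix an omnibus hypothesis. If pairwise tests were meant, a three-group Kruskal-Wallis test does not supply them.

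**No success rule is stated.** This stands. A reader might infer that the sponsor will declare the combination superior on a significant Kruskal-Wallis P. The protocol does not say so. It only expects a difference between intervention and control groups, without saying which arm is the control. The point is that the planned P cannot answer the question, not that a false claim has been planned.

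**Error inflation.** A reader might also infer that unadjusted pairwise tests after the omnibus test would raise the family-wise error to about 12%. They would not. With exactly three groups, once the omnibus null is false at most one pairwise null can still be true, so gating by Kruskal-Wallis holds the rate near 5%. The 12% belongs to ungated tests only.

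**The test is valid.** This stands too. It rejects at about its nominal rate when all arms are equal. The fault lies in the hypothesis it addresses.

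**Conclusion.** The concern holds. The only between-group outcome analysis stated is an omnibus test with one P per outcome, and this does not show whether the combination beats each component. With 3 cm and SD 3.49 it is significant in about 86% of trials at 25 per arm and 92% at 30, both when the combination equals PRF alone and when it is better than both single treatments. The percentages rest on normal data, a common SD, 1:1:1 allocation and two-sided testing. The equality of the two rates follows from the symmetry shown in step 2 and does not depend on the particular difference, SD or sample size.

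Two stronger readings are not supported. Requiring both contrasts does not push power below the stated 80% if all 90 patients are evaluable; it does if only 25 per arm are. Nor would the named contrasts establish synergy: without a neither-treatment arm, the interaction of the two treatments cannot be estimated, and what can be shown is benefit over each component.

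**What to change.** In Statistical analysis, name combined versus PRF alone and combined versus physical therapy alone as the primary contrasts. Since the plan already treats pain and functional scores by rank methods, use Mann-Whitney tests with a Hodges-Lehmann shift and 95% CI for each. Claim the combination superior only if both are significant at two-sided 0.05; no alpha split is needed when both must succeed.

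Kruskal-Wallis may stay as a supportive test, or as a gatekeeper before the pairwise tests. If success on either contrast alone may be claimed without that gate, use Holm.

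In Table 2, replace the single P column with the two differences and their confidence intervals, and label the third arm as it is described in the text.

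In the aim, say added benefit over each component in place of synergy.

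The cost is wording and a table shell, with no added patients or procedures. The downside is power: 81 to 82% to win both at 30 per arm, and about 71% if losses leave 25 per arm, below the stated 80%.

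### Ninety is both the number screened and the number recruited, the step from 25 to 90 is not explained, and the inputs size a two-group comparison rather than the planned three-group test

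*Protocol article*

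**What the plan says.** Section 2.7 of the protocol article gives the whole calculation in two sentences. The target is described as "a clinically significant difference reduction in the pain score was defined as 3 cm", with "a standard deviation of 3.49" and "probability of a Type I error of 0.05". The result and the recruitment figure follow at once: "power of 0.8 resulted in an estimated sample size of 25. Consequently, a total of 90 subjects will be recruited".

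The same section plans a Kruskal-Wallis test across the three groups for pain and function, and a Wilcoxon signed-rank test within each group. The significance rule is "The level of statistical significance is set as *P* < .05"; sidedness is not stated.

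Section 2.3 uses the same number for an earlier stage: "The treating surgeon will assess 90 patients for eligibility". Consent and then randomisation to three groups come after that step. The abstract repeats the sentence. Section 2.2 lists the exclusions, several of which (rotator cuff tear, calcific tendinitis, impingement) are found by ultrasound imaging.

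**The concern.** Three things do not fit together.

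1. **Ninety has two meanings.** It is the number screened in the abstract and section 2.3, and the number recruited in section 2.7. With imaging exclusions and a consent step in between, the two are equal only if every screened patient is eligible and agrees. The article therefore does not fix when recruitment stops.
2. **The step from 25 to 90 does not follow as written.** Section 2.7 does not say whether 25 is per group or in total. Read per group, it gives 75. The word joining 25 to 90 implies a derivation, but no multiplier or loss rate is given.
3. **The sized comparison is not named and is not the planned test.** One difference and one SD describe a two-group comparison. The article does not say which groups differ by 3 cm, or whether 3 cm is a within-group reduction. The planned between-group test is an omnibus test on three groups, whose power depends on where all three means lie.

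At stake is whether the trial keeps the 80% power it states. If a site reads 90 as a screening cap, fewer than 90 are randomised, by an unknown amount.

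**Working it through.** **Inputs from section 2.7:** difference 3 cm, SD 3.49, alpha 0.05, power 0.80. **Assumed, because not stated:** two-sided test, 1:1:1 allocation, normal data, and SD 3.49 applying to the pain measure compared.

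**Step 1. The plan's own 25, read as two equal groups.** The standardised difference is 3/3.49 = 0.860.

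- Normal approximation: n = 2 × [(1.960 + 0.842) × 3.49/3]² = 21.2, so 22 per group.
- Two-sample t-test (noncentral t): 23 per group, with power 0.81 at 23 and 0.85 at 25.
- Mann-Whitney, simulated: power about 0.78 to 0.79 at 23, 0.81 at 24 and 0.82 at 25, so 24 per group.

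As a per-group figure for two groups, 25 is close to what the inputs need and slightly above it. Other readings fit less well: a one-sided two-group test needs 17 or 18 per group, and a one-sample or paired test needs 11 to 13.

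**Step 2. From 25 to 90.** 3 × 25 = 75. Reaching 90 needs 90/75 = 1.20, that is, a 20% uplift, or equivalently a loss of 1 − 75/90 = 16.7%. Neither figure appears in the article.

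**Step 3. Power of the planned three-group test.** The largest difference is held at 3 cm and the third mean is varied. The noncentrality is λ = n × Σ(μᵢ − μ̄)²/3.49², where 3.49² = 12.18.

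- Third arm midway (0, 1.5, 3): Σ = 1.5² + 0 + 1.5² = 4.5. At n = 30, λ = 30 × 4.5/12.18 = 11.1.
- Two arms equal (0, 0, 3): Σ = 1² + 1² + 2² = 6. At n = 30, λ = 30 × 6/12.18 = 14.8.

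Multiplying λ by 3/π = 0.955, the efficiency of the rank test under normality, and using the noncentral F with 2 and 3n − 3 degrees of freedom gives Kruskal-Wallis power. Simulation with 10,000 runs per setting agrees to about 0.01.

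| Per arm | How reached | Third arm midway | Two arms equal |
|---|---|---|---|
| 30 | 90 randomised | 0.82 | 0.92 |
| 25 | 75 randomised or retained | 0.74 | 0.86 |
| 24 | 90 screened, 20% not randomised | 0.72 | 0.84 |
| 21 | 90 screened, 30% not randomised | 0.65 | 0.79 |
| 18 | 90 screened, 40% not randomised | 0.58 | 0.71 |

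The 20%, 30% and 40% are assumptions used to show the range; the article gives no screening-failure rate. The last three rows allow for no dropout after randomisation.

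In the midway pattern the margin at 30 per arm is thin: simulated power is 0.81 at 29 and 0.79 at 28.

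**The case against.** The strongest defence is that the numbers are adequate and only the wording is loose. With 90 recruited, as section 2.7 says, the planned test reaches 80% on the article's own inputs even in the least favourable pattern. That stands, and it limits the point.

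A reader might infer three stronger things, which the documents do not support:

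- *That 25 is wrong.* It is not. Section 2.7 treats pain as a nonparametric measure, so a rank test is the natural check, and that gives 24.
- *That the 80% power has no support, or that every step of the calculation fails.* At 30 per arm the Kruskal-Wallis test has about 0.82 to 0.92. The doubt arises only if 90 is a screening number or losses are appreciable. The 0.74 at 25 per arm belongs to the midway pattern; with two arms equal it is 0.86.
- *That 25 could be the total, about 8 per arm.* The missing unit allows it on paper, but a total of 90 follows immediately and there are three groups, so per group is the sensible reading.

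The defence also notes that a journal article condenses a fuller protocol, that 75 × 1.20 = 90 is an obvious bridge, that section 2.3 goes straight on to randomise each patient, and that the patient-flow figure is not shown. The absence of a loss rate alone would be a small matter on those grounds. They do not remove the conflict over 90: the article states the number at two different stages, and condensing a text does not make the stages equal.

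**Conclusion.** The point holds in this form: the article is inconsistent about what 90 counts, does not explain how 25 becomes 90, and sizes an unnamed two-group comparison while planning a three-group test. It should be fixed, but it does not show that the trial is too small.

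The size of the problem depends on which 90 is meant. If 90 are randomised and largely retained, power for the planned test is about 0.82 to 0.92 and the stated 80% is met. If 90 are screened and 30% are not randomised, it is about 0.65 to 0.79 before any dropout. These figures rest on two-sided testing, equal allocation, normal data, SD 3.49 for the pain measure, and 3 cm being the largest between-group difference. The last of these is for the sponsor to confirm.

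**What to change.** - **Fix the number.** State in the abstract, section 2.3 and section 2.7 that 90 patients (30 per arm) will be randomised and that screening continues until this is reached. Remove 90 as the number assessed for eligibility.
- **Explain the step.** State that 25 is per group. The sponsor should give the loss allowance that takes 75 to 90. The 16.7% above is back-calculated and should not be adopted unless it was the allowance actually intended.
- **Name the comparison.** The sponsor should state which groups the 3 cm compares, and whether it is a between-group difference or a within-group reduction.
- **Restate power for the Kruskal-Wallis test**, with the assumed pattern of means. If 3 cm is the largest between-group difference, this is about 0.82 to 0.92 at 30 per arm and 0.74 to 0.86 at 25 per arm.

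The cost is protocol wording only, with no patients beyond the 90 already stated. More may have to be screened to reach them. The downside is that the stated power at 25 evaluable per arm may fall below 0.8 if the third arm is expected to lie midway.
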